### 2.4 Intervention

#### 2.4.1 Intervention granules

The participants will be randomly assigned to take FA granules or placebo granules orally twice daily after meals for a total of 52 weeks. The outer packaging will be recycled and brought back to the researcher at each point.

#### 2.4.2 Granule production procedures

FA is made from multiple plants (Table 1). The granule-making procedure is shown in Figure 1.

**FIGURE 1 F1:**
[figure not shown]
Production process of the granules.

The placebo was invented and is produced by Tianjiang Pharmaceutical Co., Ltd. It consists of simple ingredients, such as raw materials and excipients, including maltodextrin bitterant and coloring matter (lemon pigment, sunset yellow pigment and caramel pigment). All the materials are of food grade, and no active ingredient is included, which excludes any notable adverse reactions or threats to the health of human beings. FA and the placebo are identical in appearance, including dosage form, aluminum-plastic packaging, and labeling. All participants receive standardized administration instructions stating “The medication has a slightly sweet taste with mild bitterness” to minimize expectation bias.

#### 2.4.3 Quality control of granule production

##### 2.4.3.1 Stability test of FA Granules

For multiple batches of FA, a similarity of more than 96% must be detected by ultra-performance liquid chromatography (UPLC), indicating that the ingredients of FA are stable and controllable. The procedure for UPLC fingerprinting of FA granule ingredients between batches is performed according to a published protocol (33, 34).

##### 2.4.3.2 Fingerprint chromatograms of FA granules

The fingerprint chromatogram of FA is obtained via high-performance liquid chromatography (HPLC) for quality control. The identification of FA compounds relies on their retention times and UV spectra compared with those of standards.

##### 2.4.3.3 Similarity analysis

This manual assessment method is carried out to determine the similarity between the placebo and FA. Twenty individuals of different ages and sexes who have neither visual (e.g., color blindness or color deficiency) nor olfactory problems are asked to independently evaluate the samples prepared versus placebo. Compared with the FA granules, the placebo granules that are completely different in color, appearance and smell are scored 0 points. Those that are completely identical are awarded 100 points. The scores of colors, appearance and smell are collected to calculate the average score. Considering the significant influence of the odor and color of the placebo, the composite score of the three variables is calculated based on the following weighting: 20% for appearance, 40% for color and 40% for odor. If the composite score is in the range of 80–100 points, this indicates a relatively high similarity with FA, and the sample can be used as a placebo for FA.

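### The placebo acceptance rule lets a good score on one attribute offset a poor score on another, so a bare pass does not show that placebo and FA match on each attribute

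*Protocol article*

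**What the plan says.** Section 2.4.3.3 of the protocol article describes a sensory comparison of placebo and FA by twenty people of mixed age and sex with normal colour vision and smell. The scale is anchored at both ends: samples "completely different in color, appearance and smell are scored 0 points", and "Those that are completely identical are awarded 100 points". The raters' scores are averaged. Because odour and colour are judged to matter most, the three attributes are combined with the weights "20% for appearance, 40% for color and 40% for odor".

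The decision rule uses the composite alone: "If the composite score is in the range of 80–100 points, this indicates a relatively high similarity with FA", and on that basis "the sample can be used as a placebo for FA". No minimum is set for any single attribute.

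Section 2.4.2, in the text below Figure 1, describes the products in stronger terms: "FA and the placebo are identical in appearance, including dosage form, aluminum-plastic packaging, and labeling".

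**The concern.** The purpose of the test is to protect the blind, and a blind can be weakened by one perceptible difference. A weighted average works the other way, because a close match in smell can make up for a poor match in colour. The section gives colour and odour the larger weights because of their influence, yet sets no floor even for these two.

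Two things are at stake. One is whether passing the test is adequate evidence for the product description in section 2.4.2. The other is the credibility of outcomes that depend on the judgement of the participant or physician: VAS, PtGA, PGA, HAQ and tender joint count, all listed as secondary in section 2.5.3. Participants take the granules twice daily for 52 weeks (section 2.4.1), so they have long exposure to the product's look and smell.

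**Working it through.** **Inputs, all from section 2.4.3.3.** Weights: appearance 0.20, colour 0.40, odour 0.40. Scale: 0 (completely different) to 100 (completely identical). Pass: composite from 80 to 100, with 80 included. Raters: 20, averaged.

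**Formula.** With attribute means A (appearance), C (colour) and O (odour):

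S = 0.20·A + 0.40·C + 0.40·O; accept if S ≥ 80.

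The 80-point mark is a chosen threshold, so the plan offers no calculation to reproduce. The scale is coherent: the weights sum to 1.00, all zeros give S = 0, and all hundreds give S = 100.

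**Lowest passing score for one attribute, with the other two at 100.** The composite may lose at most 20 points, so the minimum is 100 − 20/weight:

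- appearance: 100 − 20/0.20 = 0
- colour: 100 − 20/0.40 = 50
- odour: 100 − 20/0.40 = 50

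**Worked cases.**

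| A | C | O | S | Result |
|---|---|---|---|---|
| 0 | 100 | 100 | 0 + 40 + 40 = 80.0 | pass |
| 100 | 50 | 100 | 20 + 20 + 40 = 80.0 | pass |
| 100 | 100 | 50 | 20 + 40 + 20 = 80.0 | pass |
| 100 | 75 | 75 | 20 + 30 + 30 = 80.0 | pass |
| 50 | 75 | 100 | 10 + 30 + 40 = 80.0 | pass |
| 0 | 99 | 100 | 0 + 39.6 + 40 = 79.6 | fail |
| 100 | 49 | 100 | 20 + 19.6 + 40 = 79.6 | fail |
| 0 | 95 | 95 | 0 + 38 + 38 = 76.0 | fail |

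**Averaging over raters.** If 10 of the 20 raters score colour 0 and the other 10 score it 100, then C = (10·0 + 10·100)/20 = 50. With A = O = 100, S = 80 and the sample passes, although half the panel called the colour completely different.

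**Would a higher composite mark be enough?** At a mark of 90 the lowest passing scores become 100 − 10/0.20 = 50 for appearance and 100 − 10/0.40 = 75 for colour or odour. At 95 they are 75 and 87.5. A higher mark narrows the trade-off between attributes but does not remove it.

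**A floor on each attribute.** If A, C and O are each at least 80, then S ≥ 0.20·80 + 0.40·80 + 0.40·80 = 80. The composite then adds nothing to the decision.

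**The case against.** The case for leaving the rule alone has several sound parts.

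- **The extremes are boundary cases.** An appearance mean of 0 requires all twenty raters to give 0, and a pass then requires all twenty to give 100 for both colour and odour. Small departures fail, as the table shows. This stands, and it limits how likely the worst cases are. It does not cover the milder passing cases, such as 75 for both colour and odour.
- **The test claims little.** Section 2.4.3.3 concludes only that similarity is relatively high, and section 2.4.2 does not cite the score as its basis. This also stands. A reader might infer that the two sections contradict each other, but a minimum acceptance mark and a description of the manufactured product can both be true. What follows is narrower: a bare pass is not sufficient evidence for the description.
- **No observed score is shown.** A reader might infer that the placebo in use is visibly different or that the blind has failed. The documents do not support this. The actual scores may be close to 100, and a condensed article need not report them.
- **Participants have no product to compare with.** Each takes one product, packaging and labelling are stated to be the same, and everyone hears the same description of the taste. A difference that a rater sees side by side may go unnoticed in use. A reader might infer certain bias in favour of FA, but that would require participants or assessors to identify the arm correctly, and nothing in the documents shows that they would.
- **The primary outcome is partly protected.** Section 2.5.2 requires ultrasound confirmation as well as the classification criteria. Some indirect influence remains possible, because joints outside the mandatory set are scanned only when the participant reports symptoms (section 2.5.3). Any effect would still fall mainly on the subjective secondary outcomes.

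These points limit the consequence. They do not make a compensatory score a good rule for accepting a placebo.

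**Conclusion.** The concern holds as a criticism of the rule. The article states the full acceptance criterion, and that criterion accepts a sample scoring 0 for appearance, or 50 for colour or odour, when the other two attributes are perfect. It also accepts moderate shortfalls on two attributes at once. Passing at the mark therefore does not show a match on each attribute.

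The arithmetic is exact and rests on two readings of the text: that 80 itself counts as a pass, and that no unstated minimum applies to any attribute. The effect on trial results cannot be sized from the documents. It is a possibility for the subjective secondary outcomes, not a demonstrated bias. The change is worth making because it is cheap and would give the blinding claim direct support if the scores are good.

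**What to change.** Replace the composite-only criterion with a minimum for each of the three attribute means. A floor of 80 is a natural example because it is the article's own cut-off, and the composite can then be dropped or kept for description only. Apply the floor to the existing twenty-rater scores and to acceptance of any further placebo, and report the three means separately.

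If the placebo already in use falls below the floor on an attribute, say so as a limitation on blinding when the subjective outcomes are interpreted. Do not reclassify outcomes by placebo batch: nothing in the article links participants to batches, so that separation may not be possible.

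**Cost.** Assuming the individual attribute scores were kept, this is a re-tabulation with no new participants, visits or changes to the primary analysis. There are two downsides. The floor is a chosen value, not a derived one, and it still acts on a mean: 4 of 20 raters scoring 0 and 16 scoring 100 give exactly (4·0 + 16·100)/20 = 80. A future batch might also be rejected, and reformulating during an ongoing blinded trial needs care because it could put two distinguishable placebos into use.

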#### 2.4.4 Discontinuation criteria, adherence and concomitant therapy

Long-term medications for the treatment of underlying diseases, such as high blood pressure, are allowed. Other symptomatic treatments, such as NSAIDs, may be used if the investigators judge that they will not interfere with the assessment of the study drug. We strictly prohibit glucocorticoids, either oral or topical. All concomitant medications should be recorded in the case report form (CRF).

The trial intervention should be stopped in the following circumstances: if serious adverse events (SAEs) occur; if the patient’s condition deteriorates drastically during the trial and it cannot be ruled out that the change is related to the trial, the study should be terminated, and the necessary treatment measures should be taken for the patient; and if patients withdraw their consent.

The duration of the intervention phase and subsequent follow-up in this study are notably extensive, particularly for participants who are asymptomatic. To improve medication adherence, our approaches encompass the following aspects:

(1)   Relationship enhancement: An equitable doctor–patient rapport will be established to ensure that patients are treated with dignity and support and have an increased sense of engagement and commitment.(2)   Incentive policy: Full reimbursement will be provided for all medication and testing expenses of the participants and will be complemented by a modest financial compensation, such as transportation allowances and minor stipends. Nevertheless, ensuring that these measures do not appear to be a means of inducing participation is crucial.(3)   Technological assistance: Electronic devices and applications can be utilized to implement automated medication reminders, thereby promoting adherence to treatment regimens.(4)   Customized management: Acknowledging the diverse challenges faced by individual participants, such as work schedule conflicts, adaptable appointment schedules will be offered. For patients with limited education or advanced age, simplified educational materials, such as visual aids, can be designed. With respect to patients from different cultural or religious backgrounds, we will accommodate their diversity and offer patient-centered personalized services.(5)   Collaborative teamwork: The research team will convene for regular internal meetings to share effective strategies and address encountered obstacles, ensuring that all members have access to current information and support for enhancing patient management and communication skills.

### 2.5 Outcomes

#### 2.5.1 Demographic characteristics

Age, gender, height, weight, body mass index (BMI), current medication use, comorbidities, and family history.

#### 2.5.2 The primary outcome

The primary outcome is the time to the occurrence of RA. It is defined as the time interval from inclusion to the occurrence of RA. RA occurrence refers to the confirmation of arthritis or synovitis by ultrasound and meeting the 2010 ACR/EULAR RA classification criteria.

#### 2.5.3 Secondary outcomes

The secondary outcomes include the following:

(1)   Proportions of participants who develop RA at different observation time points.(2)   Autoantibodies: a reduction in anti-CCP or RF titer.(3)   Biochemical tests: the high-sensitivity C-reactive protein (hs-CRP) level and the erythrocyte sedimentation rate (ESR).(4)   Joint symptoms and signs: the 28-tender joint count (TJC28), 28-swollen joint count (SJC28), visual analog scale (VAS) score, morning stiffness, and other complaints, such as pain and numbness.(5)   Systemic symptoms and signs: the Patient’s Global Assessment (PtGA) score, Physician’s Global Assessment (PGA) score, Health Assessment Questionnaire (HAQ) score, and Disease Activity Score in 28 joints-C-reactive Protein (DAS28-CRP).(6)   Generic Quality of Life Inventory-74 (GQOLI-74) score.(7)   Doppler ultrasound of both hands, feet and other affected joints: (A) Mandatory joints: the radiocarpal and midcarpal joints, the distal radioulnar joint, and the 6th compartment; the metacarpophalangeal (MCP) joints in the dorsal position in the second to fifth fingers bilaterally; the proximal interphalangeal (PIP) joints and flexor tendons in the volar position in the second to fifth fingers bilaterally; and the metatarsophalangeal (MTP) joints in the dorsal position in the 2nd to 5th toes in the feet bilaterally. (B) Symptomatic joints: if patients report symptoms in joints other than those described above, the sono-rheumatologist will scan these symptomatic joints at the same time to determine whether there are any sonographic changes associated with synovitis, tenosynovitis, tendinitis, enthesitis or bursitis in these areas (Supplementary Appendix 1).(8)   Digital radiography (DR) of the hands and feet.

#### 2.5.4 Safety assessment

Safety assessment includes complete blood count (CBC), urinalysis (UA), liver function tests (LFTs) (AST and ALT), renal function tests (RFTs) (creatinine and urea), electrocardiogram (ECG), chest X-ray, and adverse events (AEs),

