### 2.6 Participant timeline

Fifty-two weeks of medical intervention will be followed by another 52 weeks of observation, for a total of 104 weeks. The time points for the measurements are as follows: screening (0 days), 4 ± 3 days, 12 ± 5 days, 24 ± 5 days, 52 ± 5 days, 78 ± 5 days and 104 ± 5 days. During the trial and follow-up, participants will be observed and evaluated via clinical and/or imaging examinations.

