#### 2.9.2 Statistical methods

Data analysis will be conducted by statisticians who are independent of the research team. All analyses are performed via the SPSS software (IBM SPSS Inc., Armonk, NY, USA). An intent-to-treat analysis will be carried out for participants who receive treatment at least once. Missing data will be imputed in accordance with the principle of multiple imputations. Continuous variables will be imputed using linear regression models, while categorical variables will be imputed using logistic regression models. Multiple imputation was performed with a user-defined number of MCMC (Markov Chain Monte Carlo) iterations. Per-protocol analysis is limited to participants who strictly adhere to the protocol and complete the trial. All the statistical tests are 2-sided, and differences are considered statistically significant at *P* values less than 0.05.

The safety dataset will also include all patients who received ≥1 dose of the intervention. The primary outcomes will be compared between the two groups via the log-rank test and the Kaplan–Meier method, and superiority will be considered with a 95% confidence interval. The secondary outcomes will be presented as frequencies, means, standard deviations (SDs), medians and ranges. To determine treatment effects, changes in the above outcomes from baseline will be analyzed via ANOVA. Group effects and influencing factors will be analyzed via analysis of covariance or a logistic regression model with covariates including sex, age, concomitant medication and measurements at baseline. Subgroup analyses will not be performed to avoid insufficient statistical power because of the small sample size. Safety will be evaluated through tabulations of AEs and coded based on the Chinese version of the Medical Dictionary for Regulatory Activities (MedDRA). Safety data will be presented with descriptive statistics at baseline, 52 weeks and 104 weeks for each group.

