#### 2.9.3 Monitoring

Any adverse events (AEs) that occur during the study period will be reported to the investigators and recorded in the CRFs. In addition to participant self-reports, abnormal laboratory findings, including routine blood tests, urine tests, liver function tests, kidney function tests and pathological electrocardiograms with clinical significance, will be recorded as AEs. AE details, including the time of occurrence, severity, causality with the intervention, actions taken, and AE outcomes, will be observed and assessed. Causalities between AEs and the FA granules will be assessed according to the WHO Uppsala Monitoring Centre System for Standardized Case Causality Assessment^2^. Any severe AEs or serious adverse drug reactions will be addressed promptly to ensure patient safety and will be reported to the principal investigator and the hospital ethics committee in a timely manner.

The trial flowchart is shown in Figure 2, and the schedules and measurements for the participants are listed in Table 2.

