**FIGURE 2 F2:**
[figure not shown]
Trial flowchart.

**TABLE 2 T2:** Time schedule and measurements.

Assessment	Visit 1	Visit 2	Visit 3	Visit 4	Visit 5	Visit 6	Visit 7
	Enrollment	4^th^ w	12^th^ w	24^th^ w	52^th^ w	78^th^ w	104^th^ w
Demographic data	×						
Family history	×						
Medical history	×						
Physical examination	×	×	×	×	×	×	×
Vital signs	×	×	×	×	×	×	×
Disease activity	×	×	×	×	×	×	×
Morning stiffness	×	×	×	×	×	×	×
TJC28	×	×	×	×	×	×	×
SJC28	×	×	×	×	×	×	×
HAQ	×	×	×	×	×	×	×
VAS	×	×	×	×	×	×	×
PtGA	×	×	×	×	×	×	×
PGA	×	×	×	×	×	×	×
GQOLI-74	×			×	×	×	×
anti-CCP	×		×	×	×	×	×
RF	×	×	×	×	×	×	×
hs-CRP	×	×	×	×	×	×	×
ESR	×	×	×	×	×	×	×
DAS28-CRP	×	×	×	×	×	×	×
CBC	×	×	×	×	×	×	×
UA	×	×	×	×	×	×	×
LFTs	×	×	×	×	×	×	×
RFTs	×	×	×	×	×	×	×
ECG	×				×	×	×
Chest radiography	×				×	×	×
DR of the joints	×				×	×	×
Ultrasound	×		×	×	×	×	×
Concomitant medication	< — — — — — — — — — — — — — — — — — — — — — — — — — — >						
Adverse events	< — — — — — — — — — — — — — — — — — — — — — — — — — — >						
Concomitant medications	< — — — — — — — — — — — — — — — — — — — — — — — — — — >						

TJC28, 28-tender joint count; SJC, 28-swollen joint count; HAQ, health assessment questionnaire; VAS, visual analog scale; PtGA, patient’s global assessment; PGA, physician’s global assessment; GQOLI-74, generic quality of life inventory-74; anti-CCP, anti-cyclic citrullinated peptide; RF, rheumatoid factor; hs-CRP, high-sensitivity C-reactive protein; ESR, erythrocyte sedimentation rate; DAS28-CRP, disease activity score in 28 joints-C-reactive protein; CBC, complete blood count; UA, urinalysis; LFTs, liver function tests; RFTs, renal function tests; ECG, electrocardiogram; DR, digital radiography.

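### No ECG is scheduled between baseline and the end of the 52-week dosing period, and two of the three post-baseline ECGs are taken off treatment

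*Protocol article*

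**What the plan says.** Four parts of the protocol article bear on this.

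- **Section 2.5.4** lists the safety measures, including "electrocardiogram (ECG), chest X-ray, and adverse events (AEs". It gives no frequency for any of them.
- **Section 2.9.3** makes ECG a source of adverse events: "liver function tests, kidney function tests and pathological electrocardiograms with clinical significance, will be recorded as AEs".
- **Sections 2.4.1 and 2.6** set the exposure period. Participants take "FA granules or placebo granules orally twice daily after meals for a total of 52 weeks", and section 2.6 adds: "Fifty-two weeks of medical intervention will be followed by another 52 weeks of observation, for a total of 104 weeks".
- **Table 2** ("Time schedule and measurements") marks the ECG row at visits 1, 5, 6 and 7 (enrollment and weeks 52, 78 and 104). Visits 2, 3 and 4 (weeks 4, 12 and 24) are blank. Blood count, urine, liver and renal tests, vital signs and physical examination are marked at all seven visits. Adverse events are recorded throughout.

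For the analysis, section 2.9.2 states: "Safety data will be presented with descriptive statistics at baseline, 52 weeks and 104 weeks for each group".

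**The concern.** A safety measure tells us about a product when it is taken during exposure. Here ECG is named as a safety measure and abnormal readings feed the adverse-event record, yet the first reading after baseline comes when dosing is ending. A change that appears early and resolves, or that causes no symptoms, leaves no trace in the scheduled data unless it is still present at week 52 or later.

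What is at stake is how an ECG result can be interpreted. If the arms look alike on ECG, that similarity describes week 52 and the off-treatment year. It says little about the preceding year of dosing. The laboratory safety tests do not share this limit, because they are repeated at weeks 4, 12 and 24.

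**Working it through.** The plan gives no figure to reproduce. The check is a count of the ECG row in Table 2 against the dosing period. The column alignment was confirmed against the GQOLI-74, anti-CCP and CBC rows, which fit the same seven visit columns.

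**Inputs**
- Dosing: weeks 0 to 52 (sections 2.4.1 and 2.6).
- Observation without treatment: weeks 52 to 104 (section 2.6).
- Visits: enrollment and weeks 4, 12, 24, 52, 78 and 104 (Table 2).
- ECG: enrollment and weeks 52, 78 and 104 (Table 2).

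| Visit | Phase | ECG | Laboratory safety tests, vital signs |
|---|---|---|---|
| Enrollment | Baseline | Yes | Yes |
| Week 4 | On treatment | No | Yes |
| Week 12 | On treatment | No | Yes |
| Week 24 | On treatment | No | Yes |
| Week 52 | End of dosing | Yes | Yes |
| Week 78 | Off treatment | Yes | Yes |
| Week 104 | Off treatment | Yes | Yes |

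**Counts**
1. Scheduled ECGs: 4, of which 4 − 1 = 3 are after baseline.
2. ECGs at visits strictly inside the dosing period: 0 of 3.
3. Post-baseline ECGs off treatment: 2 of 3, at 78 − 52 = 26 weeks and 104 − 52 = 52 weeks after dosing ends.
4. Interval from baseline to the first follow-up ECG: 52 − 0 = 52 weeks, the whole dosing period.
5. Time points in the section 2.9.2 safety summary: baseline, week 52 and week 104. The week-78 ECG is not among them.

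**Visit window.** Section 2.6 gives "52 ± 5 days, 78 ± 5 days and 104 ± 5 days". Its text counts visits in days where Table 2 counts them in weeks. That mismatch needs its own correction; weeks are used here because they agree with the 104-week total. Reading the window as ±5 days around week 52 (364 days), the ECG falls between day 359 and day 369. It may therefore be just before or just after the last dose.

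**Effect of moving one ECG.** If the week-78 reading were taken at one of the three existing on-treatment visits, the total would stay at 4. Readings during or at the end of dosing would rise from 1 to 2, and off-treatment readings would fall from 2 to 1. The longest stretch of dosing without an ECG would fall from 52 weeks to 52 − 4 = 48, 52 − 12 = 40 or 52 − 24 = 28 weeks, depending on the visit.

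**The case against.** The best defence is that nothing here is stated wrongly. Section 2.5.4 fixes no ECG frequency, so Table 2 does not conflict with it. ECG follows the same pattern as chest radiography and joint radiography, and it is present at all three time points that section 2.9.2 summarises. Physical examination and vital signs are taken at every visit, adverse events are collected continuously, and section 2.9.3 does not limit abnormal ECGs to scheduled ones. All of that stands. It means the point concerns scheduled readings only, and it is a matter of design quality. It does not explain why a safety measure that feeds the adverse-event record has no planned reading inside the exposure period.

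Several stronger readings are tempting, and the documents do not support them.

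- **That the trial cannot detect ECG effects.** A symptomatic event can prompt an unscheduled ECG. What is missing is systematic detection.
- **That the formulation calls for closer cardiac monitoring because Table 1 lists Herba Ephedrae.** No part of the article describes a cardiac effect of that component or of the formulation, so the inference would rest on outside knowledge.
- **That the dropout allowance (72 − 60 = 12 participants) measures how many lack an on-treatment ECG.** Section 2.7 applies that allowance to both arms and ties it neither to week 52 nor to intolerance.
- **That early stoppers certainly have no ECG.** Table 2 schedules none for them before week 52, but procedures at early stopping may stand in the full protocol, which this article condenses.

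**Conclusion.** The point holds as a modest design weakness that is cheap to improve. Between baseline and the end of a 52-week exposure there is no scheduled ECG (0 of 3 visits), and 2 of the 3 post-baseline readings are off treatment. A silent or transient on-treatment change would not be systematically detected. The only planned between-arm ECG comparison tied to exposure is a single reading at the end of dosing.

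This rests on Table 2 as printed, on visit times being in weeks, and on dosing ending at week 52. It concerns scheduled ECGs only and implies nothing about whether the product has any cardiac effect. Nor do the documents suggest that the sponsor intends a claim of cardiac safety: safety is described rather than tested, and section 4 presents the trial as a small pilot.

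**What to change.** In Table 2, reassign the week-78 ECG to one of the visits that already exist within the treatment period. The choice of visit should be left to the investigators. In section 2.9.2, add that time point to the safety summary; otherwise the new reading would be collected but not reported.

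The cost is a schedule amendment. There is no extra visit, and a completer still has four ECGs. Nothing is removed from the stated safety summary, because week 78 is not part of it. Two losses should be acknowledged:

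- One off-treatment ECG is given up; week 104 remains.
- Recruitment began in March 2022 and is described as ongoing, so participants already past the chosen visit cannot contribute the new reading. The report should state how many in each arm were eligible for it and how many had it.
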